# Vitamin D supplementation compared to placebo in people with First Episode psychosis - Neuroprotection Design (DFEND): a protocol for a randomised, double-blind, placebo-controlled, parallel-group trial

**DOI:** 10.1186/s13063-019-3758-9

**Published:** 2020-01-06

**Keywords:** Psychosis, First episode, Vitamin D, 25OHD, Randomised controlled trial, Positive and Negative Syndrome Scale, Mental health

## Abstract

**Background:**

People experiencing their first episode of psychosis are often deficient in vitamin D. Observational studies have reported an association between low vitamin D concentrations and poorer subsequent health outcomes in psychosis. A vitamin D deficiency in neonates and children has been linked to a later increased risk of schizophrenia and psychotic-like experiences. This trial aims to examine the effect of high-dose vitamin D supplementation on outcomes in early psychosis. We hypothesise that vitamin D supplementation will be associated with better mental health outcomes.

**Methods/design:**

The DFEND study is a multicentre double-blind placebo-controlled parallel-group trial of vitamin D supplementation in people with early psychosis. Patients with an ICD-10 diagnosis of functional psychosis will be randomised in a 1:1 ratio to receive either 120,000 IU/month of vitamin D (cholecalciferol) or a matched placebo for 6 months. The primary outcome is the total Positive and Negative Syndrome Scale (PANSS) score at the 6-month follow-up for all patients. Secondary outcomes include assessment of mood (Calgary Depression Scale), general function (Global Assessment of Functioning), cardiovascular risk (body mass index, waist circumference, C-reactive protein, cholesterol and HbA1c) and vitamin D levels at the 6-month follow-up. Additionally, 3- and 6-month total PANSS scores will be analysed for those with inadequate vitamin D levels at the baseline.

**Discussion:**

The DFEND study is the first trial to examine whether vitamin D supplementation in early psychosis is associated with better mental health outcomes. The findings of this study may help to resolve the clinical equipoise regarding the benefits and cost-effectiveness of routine vitamin D supplementation in people with psychosis.

**Trial registration:**

ISRCTN, ISRCTN12424842. Registered on 25 February 2015.

## Background

Vitamin D is a fat-soluble secosteroid obtained largely through sun exposure and, to a lesser extent, food sources such as oily fish (e.g. mackerel) and egg yolk. The best-known role of vitamin D is in regulating bone health, being essential for the regulation of calcium in the body, but latterly, important additional functions have been identified. These include links between brain function and vitamin D [1, 2] with in vitro and animal experiments demonstrating a neuroprotective effect [3]. In rodents, developmental vitamin D deficiency alters a wide range of outcomes in the adult brain, including levels of neurotransmitters relevant to schizophrenia [4, 5], while vitamin D deficiency during adulthood has been associated with changes in behaviour and brain neurochemistry [6]. In animal models, vitamin D is neuroprotective, preventing neuronal damage from inflammation and oxidative stress [7] and inducing nerve growth factor [8]. Greater ischaemic brain damage due to a stroke is seen in rodents deficient in vitamin D [9]. The long-term adverse neurobehavioural effects of maternal immune activation in offspring can be attenuated by administration of 1-, 25-hydroxyvitamin D_3_ [10]. With respect to neuropsychiatric disorders, a randomised control trial of vitamin D supplementation in those with established Parkinson’s disease showed a slower progression compared with a placebo over a 12-month follow-up [11]. Based on these findings, it has been hypothesised that vitamin D deficiency during adulthood may worsen brain-related outcomes in those with prior neuropsychiatric disorders [12].

Schizophrenia is more common in people born in the winter and spring months [13] and at higher latitudes [14], both conditions in which exposure to the sun, and so vitamin D production, is limited. In addition, dark-skinned individuals living in cold (i.e., less sunny) countries have an increased risk of schizophrenia [15]. McGrath et al. hypothesised that low levels of vitamin D in early life may be linked to an increased risk of later development of schizophrenia [16]. Indeed, a large Danish study found a higher relative risk of developing schizophrenia in adult life in neonates with low vitamin D levels [17]. Similarly, low total vitamin D_3_ levels during childhood are associated with a higher risk of psychotic experiences during adolescence [18]. A recent meta-analysis found an overall prevalence of vitamin D deficiency in patients with schizophrenia of 65% and that people with vitamin D deficiency were 2.16 times more at risk of developing the condition [19]. Diet appears to have an effect also. A large population-based study of Swedish women (*n* = 33,623) reported an association between low dietary vitamin D intake and an increased risk of psychotic-like experiences [20]. The evidence, therefore, suggests that low levels of vitamin D disrupt early brain development and may also influence later brain function.

Vitamin D deficiency is commonly defined in the UK as levels of 25-hydroxyvitamin D (25OHD) less than 25 nmol/L, insufficiency as between 25 and 50 nmol/L and sufficiency as greater than 50 nmol/L [21]. Those with established psychosis in the UK are highly likely to be vitamin D deficient, with only 14% having sufficient vitamin D levels [22]. This is true even in the early stages of psychosis. Crews et al. examined the vitamin D status of 69 people after their first episode of psychosis (FEP) along with 69 controls of similar age, sex and ethnicity [23]. Over a third had a vitamin D deficiency, while an additional 25% had a vitamin D insufficiency. Overall, the people with FEP had a nearly threefold greater risk of vitamin D deficiency than comparators. Higher vitamin D levels at presentation were associated with lower total and negative symptoms of psychosis a year later [24]. The deficiency in vitamin D seems to be unrelated to other vitamins and minerals. A meta-analysis of nutritional deficiencies in FEP produced the strongest evidence for vitamin D deficiency and some evidence for low levels of vitamin C and folate in FEP, but no evidence for deficiencies in vitamins A and E, or in minerals [25].

People with severe mental illnesses, such as schizophrenia and schizoaffective disorder, experience poor physical health and high rates of premature death [26]. They have higher levels of cardiometabolic risk factors, including higher rates of diabetes, hypertension and central obesity [27–29]. Low vitamin D levels have been associated with cardiometabolic risk in both the general population [30, 31] and in people with established psychosis [22]. Large population-based placebo-controlled studies are currently underway that will examine the influence of vitamin D supplement on general health including cardiometabolic outcomes [32].

Despite research suggesting that vitamin D is linked to brain function and schizophrenia, little high-quality evidence is available on the impact of vitamin D supplementation on outcomes for people with psychosis. Whereas several studies have given vitamin D supplements to people with psychosis [33–35], these largely focused on physical health outcomes and 25OHD concentrations and had uncontrolled research designs. However, one recent randomised controlled trial in Israel explored whether vitamin D supplementation of 14,000 IU per week for 8 weeks improved outcomes in patients with chronic schizophrenia who were being treated with clozapine, but found no improvement in mental health, cognitive or metabolic outcomes [36]. To our knowledge, there have been no trials examining vitamin D supplementation in FEP. If vitamin D confers a positive neuroprotective effect and improves outcomes in psychosis, the first episode may be the ideal window of opportunity.

Clinical equipoise, therefore, persists as to whether routine vitamin D supplementation in early psychosis can improve mental or physical health outcomes. This paper describes the study protocol for the DFEND study, which is a randomised double-blind placebo-controlled parallel-group trial evaluating the impact of 6 months of vitamin D supplementation on Positive and Negative Syndrome Scale (PANSS) outcomes in people with early psychosis.

## Method/design

### Aims and objectives

The primary objective of the trial is to determine whether adding a monthly supplementation of 120,000 IU of vitamin D_3_ (cholecalciferol) to the standard treatment is more efficacious than a placebo in improving outcomes (PANSS) at the 6-month follow-up after an FEP. Secondary objectives are to examine the total PANSS score at 3 months, PANSS sub-scores at 3 and 6 months, along with a broader range of clinically relevant outcomes including Global Assessment of Function (GAF), the Calgary Depression Scale (CDS), cardiovascular risk markers and 25OHD concentrations. Here we report the DFEND study protocol according to SPIRIT guidelines (see Supplementary Material Additional file 1 for the SPIRIT Checklist).

### Setting

The study will take place in facilities run by English mental health trusts, which are part of the National Health Service (NHS) in the United Kingdom. Participants will be identified and recruited from clinical mental health services, including early intervention services, home treatment teams, general and forensic inpatient units, and outpatient community teams. The study is sponsored jointly by Kings College London (London, UK) and the South London and Maudsley NHS Foundation Trust (London, UK).

### Ethics

The trial will be conducted in compliance with the principles of the Declaration of Helsinki (1996), the principles of Good Clinical Practice laid out by the International Conference on Harmonisation (ICH-GCP) [37] and in accordance with all applicable regulatory requirements including but not limited to the Research Governance Framework and the Medicines for Human Use (Clinical Trial) Regulations 2004, as amended in 2006 and any subsequent amendments.

The protocol and related documents have been approved centrally by the National Research Ethics Committee, London Dulwich (reference 14/LO/1588), and has received clinical trial authorisation from the Medicines and Healthcare Products Regulatory Agency (MHRA) (reference 14523/0261/001–004). Recruitment will not begin at study sites until local approvals have been obtained. It has also been approved by the Health Research Authority (HRA, reference IRAS 147978) and registered online (ISRCTN12424842, 10.1186/ISRCTN12424842, registered on 25 February 2015, accessed 28 January 2019).

### Eligibility criteria

The study population is patients experiencing FEP, defined as presenting to health services with symptoms of psychosis within the last 3 years. A minimum level of symptoms or PANSS score is not required to take part, and patients can be enrolled during a period of stable remission. Patients must have the capacity to give written consent, which is determined by the delegated team members in conjunction with treating clinicians if needed.

#### Inclusion criteria

Aged between 18 and 65 years old, including women of child-bearing ageHaving a diagnosis of functional psychosis defined according to ICD-10 criteria for psychosis (codes F20–29 and F30–33)Willing to refrain from taking multivitamin or non-study vitamin D supplements that exceed 400 IU per day throughout the studyWilling to give a blood sample to assess vitamin D levels at baselineAble to and have given written informed consent

#### Exclusion criteria

Known intolerance of vitamin D_2_ or D_3_ or known allergy to any of the trial medicationsTaking vitamin D supplements at a dose exceeding 400 IU per dayHaving taken cardiac glycosides, calcium channel blockers or oral, intramuscular, or intravenous corticosteroids, bendroflumethiazide, isoniazid or rifampicin in the past monthKnown active tuberculosis, sarcoidosis, hypo- or hyperparathyroidism, past or present nephrolithiasis (renal stones), suspected or diagnosed hepatic or renal dysfunction, any malignancy other than non-melanoma skin cancer not in remission for ≥3 years, or calcium disordersBaseline corrected serum calcium >2.6 mmol/LKnown history of hypercalcaemiaPregnant or breast-feeding women, or women planning a pregnancyLacking the capacity to provide written informed consentInsufficient English to complete the core assessments with the available assistance

### Outcomes

All outcomes and time points are specified in Fig. 1.

**Fig. 1 Fig1:**
[figure not shown]
SPIRIT figure. Schedule of enrolment, interventions, and assessments in the DFEND Study. *Blood sampling for calcium levels (including a parathyroid hormone test if hypercalcaemic) will always be done at month 3 but can be done at all monthly visits if patient reports nausea or vomiting. NOS Nottingham Onset Schedule, PANSS Positive and Negative Syndrome Scale, GAF Global Assessment Functioning, CDS Calgary Depression Scale, OPCRIT Operational Criteria, IPAQ International Physical Activity Questionnaire, SIMPAQ Simple Physical Activity Questionnaire

#### Primary outcome

The primary outcome is symptom severity, as assessed via total PANSS scores at 6 months after randomisation [38]. PANSS assesses symptom severity across three domains: positive symptoms (seven items), negative symptoms (seven items) and general psychopathology (16 items) [38]. A total PANSS score is derived by summing scores across the three domains. Scores range from 30 to 210, with higher scores depicting greater symptom severity. In terms of reliability, α = 0.73, 0.83 and 0.79 for the positive, negative and general psychopathology scales, respectively [38]. All researchers will undergo two thorough stages of in-house PANSS training. Firstly, trainee researchers will watch and rate two PANSS training videos on two separate occasions, followed by feedback and discussion with the trial manager. Secondly, trainee researchers will shadow an experienced member of the team and observe real-world PANSS interviews, after which they will rate the interview to become familiar with the rating scale. Researchers will then be permitted to conduct the PANSS assessments independently. Researchers will also be required to attend a training session every six months to maintain their reliability throughout the trial.

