### Randomisation

An online randomisation service will be provided by King’s Clinical Trials Unit (King’s College London, London, UK). Randomisation will take place after collection of baseline measures. Randomisation will be stratified according to ethnicity (white or other) at a 1:1 ratio with randomly varying block sizes of 2–4. While there are no known predictors of PANSS scores in our target population, the concentration of vitamin D in blood varies by ethnicity [47], and we hypothesize that this concentration mediates any effect of vitamin supplements.

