### Statistical analysis

Full details of the statistical analyses will be specified in a statistical analysis plan written in collaboration with the trial statisticians.

Descriptive analyses, recruitment rate, consent rate, loss to follow-up, departures from randomised treatment and the prevalence of serious adverse events post-randomisation will be reported and summarised by treatment arm over the course of the study. All causes of withdrawal from the randomised treatment will be reported.

Analyses will be carried out by the trial statistician, who will remain blinded until all analyses are completed. The analysis of vitamin D concentrations in blood samples taken at 6 months, which is a secondary outcome, will be carried out after all other analyses are completed, as there is a high expectation that the mean concentration will be higher in the intervention group.

An intention-to-treat analysis of the effect of vitamin D supplementation on the primary PANSS outcome will be conducted using linear mixed modelling. All the available follow-up data from the randomised participants will be modelled. The analysis model will include treatment arm (vitamin D or placebo), time (3 or 6 months), baseline PANSS and randomisation stratifier (ethnicity) as explanatory variables. The model will also contain a subject-varying random intercept to account for any correlation between the repeated measures. Treatment effects on the other secondary outcomes at 6 months will be assessed using similar modelling techniques, employing generalisations to non-normal data where necessary.

To address the secondary research objectives, we will also estimate treatment effects for the subpopulation who were vitamin D insufficient at baseline in terms of primary and secondary outcomes, except for 25OHD blood concentrations, by including relevant interaction terms between baseline vitamin D insufficiency status and treatment group in the statistical models.

We expect that some data will be missing in the post-treatment outcome variables. The linear mixed modelling analyses are based on maximum likelihood and will provide valid inferences under a missing-at-random missingness mechanism. We will explore predictors of missingness. If deemed suitable for adjustment, we will include these as explanatory variables in the analyses. If post-randomisation variables are identified, a multiple imputation model will be considered instead [49].

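### The stated primary model has no site term and PANSS raters are released without a stated agreement criterion; the cost is some precision, not bias

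*Protocol article*

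**What the plan says.** All places are in the protocol article.

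- **Design (abstract, Methods/design).** "The DFEND study is a multicentre double-blind placebo-controlled parallel-group trial of vitamin D supplementation in people with early psychosis". The numbers of sites and raters are not given.
- **Rater training (Primary outcome).** In the first stage, "trainee researchers will watch and rate two PANSS training videos on two separate occasions, followed by feedback and discussion with the trial manager". In the second, trainees shadow an experienced colleague at real interviews, "after which they will rate the interview to become familiar with the rating scale". The release step follows: "Researchers will then be permitted to conduct the PANSS assessments independently". For upkeep: "Researchers will also be required to attend a training session every six months to maintain their reliability throughout the trial". No pass mark, comparison with a consensus score or agreement statistic is attached to any step.
- **Reliability figures (Primary outcome).** "In terms of reliability, α = 0.73, 0.83 and 0.79 for the positive, negative and general psychopathology scales, respectively". These come from the cited scale literature.
- **Randomisation.** "Randomisation will be stratified according to ethnicity (white or other) at a 1:1 ratio". Site is not a stratifier.
- **Primary model (Statistical analysis).** "The analysis model will include treatment arm (vitamin D or placebo), time (3 or 6 months), baseline PANSS and randomisation stratifier (ethnicity) as explanatory variables". A subject-level intercept is the only random effect named.
- **Blinding (Assignment of intervention).** Outcome assessors and trial statisticians are blinded.

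**The concern.** PANSS total is the sum of 30 interviewer-rated items, and the sample size section works with a difference of about 6 points. One point of leniency or severity on six items moves a total by that much. Ratings were made at several sites by staff trained in house. Recruitment ran from January 2016 to June 2019, so differences in rating habit between sites and over time are plausible.

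Two features leave that variation unmanaged in the text as written. First, nothing ties release to measured agreement. The alphas, read in the usual way, show how well items within a subscale hang together and say nothing about whether two of this trial's raters would give a patient the same score. The same article does quote intra-class coefficients for the GAF, a secondary outcome. Second, variation between sites stays in the residual because site is in neither the stratification nor the listed model.

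At stake are the width of the confidence interval and, if the result is null, the reader's ability to judge how well the primary outcome was measured.

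**Working it through.** **Inputs from the article (Sample size).** SD 15.0; alpha 0.05, taken as two-sided; 240 randomised with 20% attrition, so 240 × 0.8 = 192 analysed, 96 per arm.

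**Assumptions, because the article gives no figures.** Share *s* of PANSS variance due to site or rater: 5% and 10%. For the simulation: six unequal sites.

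**1. Reproduce the plan's figures.** Detectable difference = SD × (1.960 + 0.842) × √(4/N) at 80% power.
- N = 200: 5.94; N = 180: 6.26 (5.97 and 6.30 by the t distribution). The article gives 6 to 6.3, so it reproduces.
- N = 192: 15 × 2.802 × √(4/192) = 6.07.
- Power for 6 points at N = 192: standard error 15 × √(4/192) = 2.165; 6/2.165 − 1.960 = 0.811; power 79.1%.

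**2. Add a site term, with the SD of 15 already containing the site share.** Residual SD = 15 × √(1 − s), so the standard error falls by 1 − √(1 − s).

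| s | Residual SD | SE reduction | Detectable difference | Power for 6 points |
|---|---|---|---|---|
| 0 | 15.00 | – | 6.07 | 79.1% |
| 5% | 14.62 | 2.5% | 5.91 | 81.1% |
| 10% | 14.23 | 5.1% | 5.75 | 83.2% |

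**3. Sensitivity: the SD of 15 excludes the site share and the model ignores it.** Total SD = 15/√(1 − s), which is 15.39 or 15.81. The detectable difference becomes 6.22 or 6.39, and power for 6 points 77.1% or 74.8%. A site term brings this back to about 79.1%, again a gain of about 2 to 4 power points.

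**4. Check for bias.** Simulation of 8,000 trials per setting, N = 192, blocks of 4 ignoring site, *s* = 5%, 10% and 20%, site omitted from the analysis. For a true difference of 6 the mean estimate was 5.99 to 6.02. With no true difference the rejection rate was 0.049. Adding site raised simulated power from 79.5% to 79.8% at *s* = 5% and from 79.8% to 82.0% at *s* = 10%, so the realised gain can be smaller than in step 2.

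**5. What baseline adjustment already does.** Steps 2 to 4 leave baseline PANSS out. In the planned model, baseline takes up part of any site or rater level that is stable from baseline to follow-up. It does not take up drift or a change of rater. The gains above are therefore towards the upper end for their assumed shares.

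**The case against.** The strongest reply is that nothing here threatens validity. Allocation is individual and central, assessors are blinded, and chance imbalance between sites is already reflected in the standard error. That stands. A reader might infer that rater and site differences feed directly into the arm comparison and distort it. The design does not support this, and step 4 of the working shows no bias.

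A second reply is that this is a condensed article. The full protocol (version 10.1), a training manual or the SAP may hold a pass mark or a site term. That also stands. A reader might infer that a trainee whose ratings are far from consensus is released anyway, or that reliability is never measured. The text says neither: it is silent on a criterion, and it does describe feedback and six-monthly sessions. What remains is that the release sequence and the covariate list are written out step by step, and as written they contain neither element.

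A third reply concerns size. One might argue that poor agreement would cut power from 80% to 72%, by supposing that the planning SD of 15 reflects an inter-rater ICC of 0.85 and that this trial achieves 0.70. Neither ICC is in the article, and the sum uses an SD not adjusted for baseline. In the same scenario with baseline adjustment, and rater error independent across visits, an assumed baseline-to-6-month correlation of 0.4, 0.5 or 0.6 gives power of 77%, 80% or 83% for 6.07 points. The 72% figure should not be relied on.

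Finally, the Randomisation section gives a reason for its choice: no known predictors of PANSS in this population, whereas vitamin D concentration varies by ethnicity. That is a fair defence of the stratifier. It does not stop the analysis from adjusting for site.

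**Conclusion.** This is a modest, inexpensive improvement and not a design fault. The primary model as listed omits site in a multicentre trial with a rater-scored outcome, and the rater release step carries no stated agreement criterion. The treatment estimate stays unbiased and type I error is kept. The loss is precision: about 0.16 to 0.32 points of detectable difference (6.07 against 5.91–5.75) and about 2 to 4 power points for a 6-point effect. That assumes a 5–10% site or rater share within the SD of 15, and the loss is smaller to the extent that baseline PANSS already absorbs stable site levels. The share, the number of sites and inter-rater agreement are not in the article, so the size can only be given as a range.

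The two parts are separate. A site term does not repair disagreement between raters within a site, and an agreement check does not change the estimate; it documents how well the outcome was measured. The article does not suggest that raters change between a participant's visits, so a same-rater rule would answer no stated defect.

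**What to change.** 1. **Prespecify site in the primary mixed model before unblinding**, as a random intercept or as a fixed effect with small sites pooled. The Statistical analysis section keeps the statistician blinded until all analyses are complete, so this can be added without knowledge of results. If the SAP already contains it, nothing more is needed. Cost: one model term, a few degrees of freedom out of about 192 participants, and a pooling rule for small sites.
2. **Measure and report rater agreement.** Calculate each rater's agreement with the consensus score from the training-video ratings, where these were kept. Apply the same check at any six-monthly session still to come, and report the ICC with the primary result. Cost: some scoring work.

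The second step has a limit. Recruitment closed on 14 June 2019 and follow-up was planned to end in December 2019, so an agreement check can no longer affect baseline ratings and may affect few or no follow-up ratings. Its remaining value is to show how well the primary outcome was measured.
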